**Figure 4 F4:**
[figure not shown]
ABATON patient app screenshots, displaying questionnaire overview on the left and graphical display of RAPID-3 history on the right. RAPID 3 routine assessment of patient index data-3. Translations: Ausfüllen, Fill in; Datum, date; Fällige Fragebögen, due questionnaires; Fragen, questions; Historie, history; Hohe Krankheitsaktivität, high disease activity; In Klinik auszufüllen, to be answered in the outpatient clinic; Meine Monitorings, my monitorings; Moderate Krankheitsaktivität, moderate disease activity; Nahe Remission, close remission; Niedrige Krankheitsaktivität, low disease activity.

### Routine Clinical Assessment

Local rheumatologists perform the routine patient visit including DAS-28 joint count, standard venous blood withdrawal for CRP analysis, recording of patient-perceived disease activity (VAS 0–10) and physician global assessment (PGA) (VAS 0–10).

### Data Collection and Web-Based Study Module

Data is collected using the ABATON platform with the study module (Figure 5) and the web-based patient app, which allow intuitive and rapid data entry. In addition to the patient-entered data via the application, general patient-related clinical data such as disease duration, previous and current medication is added manually to the ABATON platform by the local study personnel (Table 1). Furthermore, all rheumatologists (local rheumatologist and two tele-rheumatologists) enter their therapeutic decision for each patient and visit (T0 and T1) via the web-based application. ABATON allows a quick assessment of all study patients and the completeness status of related data points (monitoring, entries of health care professional, etc.).

**Figure 5 F5:**
[figure not shown]
Screenshot of web-based study module displaying overview of the patients' statuses.

### Primary and Secondary Outcomes

Primary outcome will be the agreement of therapeutic suggestions of patients and tele-rheumatologists compared to the gold-standard, the therapeutic decision by the local rheumatologist.

Secondary endpoints will include: the overall usability and acceptance of the study app [measured by the System-Usability Scale by patients and physicians (SUS) and Net-Promoter Score (NPS)]; the agreement of patient- vs. physician-performed joint count; agreement of venous and capillary based CRP; willingness to perform CRP quick test among patients (NPS); travel time to rheumatologist (hours); agreement of tele-rheumatologist and local rheumatologist-based clinical disease activity index (CDAI); agreement of patient-based disease activity score (Auto-DAS28-CRP) and local rheumatologist-based DAS-28 CRP; change in patient's confidence for self-management (Patient Activation Measure, PAM) over time; willingness to substitute routine appointments for telemedicine appointments among patients (NPS); change of perceived assessment accuracy of rheumatologists and patients concerning patient disease activity since the last appointment (VAS 0-10).

### Sample Size

Due to the exploratory character of the trial, no formal sample size calculation was performed. A number of *n* = 120 patients was estimated to be sufficient to assess the primary outcome. With only two study visits 3 months apart, the estimated dropout will be low. However, even a moderate dropout rate of 20% would lead to a number of 96 patients to be analyzed.

### Measures and Questionnaires

#### Auto-DAS28-CRP

To assess disease activity, the CRP-based DAS-28 will used (16). The DAS28-CRP is a composite score comprising the acute phase parameters CRP, the patient reported disease activity in terms of the patient global assessment (PtGA) as well as the TJC and the swollen joint count SJC. The PtGA is assessed by a verbally administered numeric rating scale ranging from 0 to 100, asking for the patient's disease activity in the past 7 days. TJC and SJC comprise 28 predefined joints and are usually performed by a trained physician (16). In this study, an Auto-DAS28-CRP will be performed: The DAS-28 subdomains TJC and SJC will be assessed by the patient himself and then entered into the app, together with the PtGA at T0 and T1 and the result of the semi quantitative test (positive/borderline/negative). For calculation purposes we will use a pragmatic approach and enter CRP values of 0 μg/mL for negative results, 6 μg/mL for marginal values and 20 μg/mL for positive values. The values were chosen considering the manufacturers thresholds and a meaningful impact on the DAS28-CRP calculation.

#### Clinical Disease Activity Index (CDAI)

As an alternative RA specific disease activity score, the CDAI was chosen as a CRP-independent and purely clinical index. The CDAI includes the 28 joint count examination, the PGA and the PtGA and is used both in clinical practice and in clinical trials. It has been shown to be valid an sensitive for the assessment of RA activity and treatment response (17).

#### Routine Assessment of Patient Index Data (RAPID-3)

The routine assessment of patient index (RAPID-3) is a validated patient-reported outcome measure (PROM) for RA patients (18), evaluating the patient's physical function, pain, and global health. It's electronic version is validated (19).

#### Patient Activation Measure (PAM)

The PAM13 is a 13-item measure that assesses patient activation, including their knowledge, skills and confidence to manage their own health and well-being (20). The 13 items are answered on a Likert scale from 1 to 4 (strongly disagree to strongly agree). This questionnaire reflects the four stages of activation. Level 1: Patients believe that their role is important (item 1 and 2); level 2: patients have the confidence and knowledge to take an active part (items 3–8); level 3: patients take action and participate actively (items 9–11); level 4: patients have integrated their active role into their everyday life and hold on to it in stressful situations (items 12–13). Higher PAM scores indicate higher patient activation. The validated German version PAM13-D will be used (21).

#### System-Usability Scale (SUS)

Usability and acceptance of the ABATON app will be tested using the SUS (22). The SUS consists of a 10-item questionnaire answered on a scale from 1 to 5 (strongly disagree to strongly agree) (22). The scores for each question are added and multiplied by 2.5 to transform to a 0–100 scale. Scores above 68 are considered above average (22).

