Auto-DAS-28 (CRP)	Disease activity	Patient	T0 and T1	5
PAM-13	Patient activation	Patient	T0 and T1	13
TELERA-set		Patient	T0 and T1	5
System-usability-scale	Usability and acceptance of ABATON app	Patient	T1	10
Net-Promoter-Score	Willingness of patients to recommend ABATON app	Patient	T1	1
Medical history	Disease duration, current and prior treatments, CRP-value.	Local rheumatologist	T0	3
Treatment question	Treatment decision (escalation, de-escalation or no change)	Local rheumatologist, Tele-rheumatologist 1, Tele-rheumatologist 2	T0 and T1	3

*CRP, c-reactive protein; PAM-13, patient activation measure 13; RAPID-3, 3 routine assessment of patient index data-3*.

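### The SUS scoring rule contradicts its own range: ten items scored 1–5, summed and multiplied by 2.5, run from 25 to 125, not 0 to 100

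*Protocol article*

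**What the plan says.** The System-Usability Scale (SUS) section of the protocol article gives the instrument's format: "The SUS consists of a 10-item questionnaire answered on a scale from 1 to 5 (strongly disagree to strongly agree"). It then gives the scoring rule, "The scores for each question are added and multiplied by 2.5 to transform to a" 0–100 scale, and the reference value, "Scores above 68 are considered above average". It describes no subtraction, recoding or reversal of items before they are added. Table 1 also lists ten questions for the SUS, completed at T1, so the item count is consistent.

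Under Primary and Secondary Outcomes, usability and acceptance of the app is a secondary endpoint, "measured by the System-Usability Scale by patients and physicians (SUS) and Net-Promoter Score (NPS").

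**The concern.** The article did not leave scoring to another document. It states a rule, and the rule does not produce the range given in the same sentence. An analyst who followed the words would obtain totals that can never fall below 25 and can exceed 100, and would then compare them with a reference value meant for a 0–100 scale.

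At stake is the interpretation of app usability in a study whose stated aim includes feasibility. The value 68 is the only SUS reference the article offers. If scores were shifted upwards, an app that respondents rated as middling would be reported as above average. The error would run in one direction, in favour of the app.

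**Working it through.** **Inputs** (all from the SUS section; item count also in Table 1): k = 10 items; response x from 1 to 5; multiplier 2.5; stated range 0–100; reference value 68.

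**1. Range under the written rule.** Score = 2.5 × sum of x.
- Minimum: 10 × 1 × 2.5 = 25.
- Maximum: 10 × 5 × 2.5 = 125.

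The stated 0–100 is not reproduced.

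**2. What would reproduce it.**
- Recode each item to 0–4 first: 10 × 0 × 2.5 = 0 and 10 × 4 × 2.5 = 100. This gives the stated range exactly.
- Keep 1–5 and change the multiplier so that the maximum is 100: 100 / 50 = 2.0, and the minimum is then 10 × 1 × 2.0 = 20. This does not give 0–100.

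Of the two variants tried, only the recoding fits both the multiplier and the range, so the missing step is the recoding to 0–4.

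**3. Size of the shift, if all items point the same way.** Recoded score = 2.5 × (sum of x − 10) = written score − 25. The shift is a constant 25 points.
- A written score of 68 equals 68 − 25 = 43 on the 0–100 scale.
- The reference value of 68 on the 0–100 scale corresponds to 68 + 25 = 93 under the written rule.
- In terms of the item mean, the written rule passes 68 at 68 / 25 = 2.72, below the midpoint of 3. The recoded rule passes it at 2.72 + 1 = 3.72.
- Raw sums are whole numbers, so the two rules disagree for sums of 28 to 37. A sum of 28 gives 70 as written and 45 recoded; a sum of 37 gives 92.5 as written and 67.5 recoded.

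**4. The neutral respondent.** Answering 3 throughout gives 10 × 3 × 2.5 = 75 as written, above 68. Recoded, it gives 10 × 2 × 2.5 = 50, below 68. This example does not depend on item direction, because 3 − 1 and 5 − 3 are both 2.

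**5. Sensitivity to item direction (assumption; the article does not give item wording).** Let r of the 10 items be reverse-worded and left unrecoded. The most favourable answers score 2.5 × [5(10 − r) + r] = 125 − 10r, and the least favourable score 2.5 × [(10 − r) + 5r] = 25 + 10r.

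| r | Least favourable answers | Most favourable answers |
|---|---|---|
| 0 | 25 | 125 |
| 1 | 35 | 115 |
| 2 | 45 | 105 |
| 3 | 55 | 95 |
| 4 | 65 | 85 |
| 5 | 75 | 75 |

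With r = 0 the written rule keeps the ranking of respondents and only shifts the level. As r rises the spread shrinks, and at r = 5 the best and worst answers both score 75 and cannot be told apart.

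**The case against.** The strongest reply is that this is a condensed description. The article names the 0–100 target and cites the source of the instrument, and item-level scoring is commonly left to a fuller document that is not shown. Totals above 100 would also alert whoever ran the analysis. This limits what can be said about the actual analysis, which may well be correct. It does not remove the contradiction, because the article states a rule and that rule is wrong.

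Two stronger readings are tempting.

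- A reader might infer that the comparison with 68 is invalid in this trial. The documents support that only if the sentence is carried out literally, and nothing shows that it is.
- A reader who knows the instrument might say that the rule counts negatively worded items in the app's favour. The article says nothing about item wording, so this can stand only as the assumption in step 5 of the working.

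Nor does the article say that the app computes the SUS score itself. It says only that the questionnaires were pre-configured and that a dashboard shows frequently entered scores.

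On weight, the objection is right. The SUS is a secondary endpoint in an exploratory trial, the order in which endpoints are listed implies no hierarchy, and no test or success criterion is tied to 68.

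**Conclusion.** Wrong as written; it should be fixed. That the stated rule gives 25–125 and not 0–100 is exact and needs no assumption. Under literal use, an all-neutral respondent scores 75 instead of 50 and moves from below to above the reference value, whatever the item direction.

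The uniform excess of 25 points rests on two assumptions: that the rule is applied literally and that all items point the same way. If some items are reversed, the score also loses its power to separate good from poor ratings, completely so at five of ten.

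The primary outcome, agreement of treatment decisions, is unaffected. The documents do not show that any SUS result has been or will be miscalculated, so the case is for a correction and a check, not for doubting the trial.

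**What to change.** Replace the scoring sentence with one to this effect: each item is recoded to 0–4 so that higher is more favourable (response minus 1, or 5 minus response for any negatively worded item), the ten recoded items are summed (0–40), and the sum is multiplied by 2.5 (0–100). The value 68 can then be used as stated.

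Confirm that the SUS analysis, wherever the score is computed, follows this rule. If it does not, rescore from the item responses. Enrolment began in August 2021, so some T1 questionnaires may already be in hand.

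The cost is one sentence and one check. No new data are needed, provided that the item-level answers are kept.

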#### Net-Promoter-Score (NPS)

The NPS measures the willingness of the participants to recommend the ABATON app to another patient (23). Participants answer using a 11-point numeric rating scale (0 not at all likely, 10 extremely likely). Answers between 0 and 6 are summarized as detractors, 7–8 as passives and 9–10 as promoters. The NPS is calculated by subtracting the percentage of detractors from the percentage of promoters (23).

### Semi-structured Telephone Interviews

To explore patient acceptance, app compliance, change in patient's confidence for self-management and change in patient's perceived self-efficacy, complementary qualitative interviews are conducted with patients (*n* = 10) and providers (*n* = 4). The interviews are held via telephone, using a semi-open interview guide. The interviews are audio-recorded, transcribed verbatim and analyzed using qualitative content analysis (24). To achieve intersubjectivity and consistency, the analytical work is carried out within the group for qualitative research of the Centre for Health Services Research Brandenburg using the analysis software MAXQDA.

### Statistical Analysis

Interrater reliability will be calculated by Cohen's kappa. For this exploratory study, 120 patients with RA will be recruited. Correlation analyses will be used to assess the agreement of patient- vs. physician-based DAS-28 and the clinical decisions of patient vs. tele-rheumatologists and face-to-face rheumatologist. Multivariable regression analyses will be performed to assess changes in self-management and self-efficacy and their influential factors over time. Analyses will be adjusted for potential confounders such as age, disease duration, disease activity and the number and type (conventional disease modifying antirheumatic drugs (DMARD), biological DMARD or targeted-synthetic DMARD) of previous treatments.

## Results

Enrolment of participants started in August 2021. Recruitment of 120 patients and follow-up assessments are expected to be completed by June 2022. Thus far, patient feedback has been positive. Patients seem to appreciate the ability to receive empowering in-depth information about disease evaluation and to independently assess their disease activity.

## Discussion

TELERA is an exploratory study to assess the feasibility and performance of asynchronous telemedical assessments of patients with RA. The overall aim is to move current rheumatology care toward a needs-based approach with the help of remote care. Currently, the number of new rheumatologists is declining (3) and it still takes multiple months for patients to see a rheumatologist (25). However, we could demonstrate that the majority of patients and rheumatologists agreed that patients in remission do not need to be seen in person (26). The recently published EULAR guidelines highlight the importance of self-management skills and potential of mobile apps to improve the clinical care of people with RA (27). Importantly, Thurah et al. could previously demonstrate in a RCT that a remote care approach was safe and not inferior to conventional management in RA (28). In this RCT, 294 patients with RA were requested to complete ePROs and a CRP measurement each 3–4 months. The CRP measurement was however not performed by patients themselves, no joint-count was carried out and ePRO questionnaires were completed before tele-health follow-ups, which were synchronous. Based on our previous work (9), we chose a 1 week ePRO frequency, providing rheumatologists and patients with continuous disease activity data and including self-sampling (26, 29). Furthermore, we wanted to see if our study confirms previous results showing a significant increase in patient activation (PAM) after using an RA monitoring app (12). The benefits of an intensive RA telemonitoring strategy have also been demonstrated by Salaffi et al. (13), who could show that patients with early arthritis reach the state of remission more often and faster when receiving frequent telemonitoring and treatment adjustments according to a standardized treatment protocol rather than standard of care. In our opinion, the simple shift from physical in-person visits to virtual visits will not result in a significant liberation of resources and in particular time of rheumatologists. Nevertheless, asynchronous visits give patients and rheumatologists the freedom of time and place. By using a combination of objective and subjective markers for disease-activity self-assessment, patients can inform their rheumatologists in detail about their health status. Based on this remote patient-generated information, rheumatologists should continuously adapt the follow-up strategy incorporating remote care strategies (30): in case a patient achieves remission after therapy induction, the subsequent ePRO frequency could be extended and a remote follow-up (i.e., telephone call) after 3 months could be scheduled instead of a face-to-face meeting. Web based asynchronous home telemonitoring is already an integral part in the care of other chronic diseases such as diabetes and heart disease (31), as well as inflammatory bowel disease (32) and has great potential in rheumatology (33). To the best of our knowledge, this is the first trial evaluating the potential of asynchronous telemedicine visits based on patient-based joint counts, self-performed CRP and ePROS in RA patients. Furthermore, it is the first study comparing treatment decisions of patients, rheumatologists and tele-rheumatologists. A major strength of this study is the early patient involvement. The study design and protocol was designed in close cooperation with three official patient research partners of the German League against Rheumatism (Deutsche Rheuma-Liga Bundesverband e.V.) who commented on and edited the draft version and approved the final study protocol. We deliberately chose a risk-adverse study setting, where participation has only a minimal impact on clinical care (rheumatologists have access to ePROS in-between visits). This study design has some limitations. Patients eligible for the study need to be in possession of a smartphone and need to have a sufficient level of understanding and dexterity to use the app, resulting in exclusion of some elderly or cognitively impaired, as well as underprivileged patients without smartphone or network access. This is a general limitation in app-based remote health care monitoring and will most probably change within the next decades. Similary, the chose time-frame limits the analysis to two appointments per patient.

Due to the exploratory study character, patients will not be stratified by disease duration, activity or previous treatments. Analyses will however be adjusted for these possible confounders. Furthermore subgroup analyses will be performed to assess potential differences between patients in remission or with active disease. Also, remote evaluation can be difficult in patients with recent treatment changes who have experienced some improvement but still have active disease. For these cases, remote rheumatologists receive information on previous therapies including recent changes.

The usage of semi-quantitative CRP tests provides only a certain degree of accuracy. However, this is a simple testing system that could be performed at home without the need of extensive equipment. Further, after discussing the options with patients, it seemed more important to receive approximate results in a short period of time than exact results after multiple days.

## Conclusion

Anticipating an aggravation of the current shortage of rheumatologists, we are convinced that it offers even greater value to empower patients to assess their disease activity more professionally and independently use quick CRP tests, ePROs and a self-performed joint count. Ultimately, this patient empowerment in combination with technological innovation could result in more need-adapted visits and increase of remote care.

## Ethics Statement

The studies involving human participants were reviewed and approved by Ethical Committee of the University Clinic of Tuebingen (# 4442020). The patients/participants will be required to provide written informed consent to participate in this study.

